#### Primary outcome measures

2.5.1

We will formulate standards for evaluating the efficacy of OMS in accordance with the Standards for Diagnosis and Treatment of Traditional Chinese Medical Diseases. The specific evaluation criteria for the efficacy are as follows:

1.Cure: the twitching of the eye cells or facial muscles disappears without recurrence within half a year;2.Effective: the spasm level of the eye cells or facial muscles is reduced, the number of twitching is reduced, and the time between twitching is shortened;3.Ineffective: The degree of spasm of the ocular muscles has not improved. All patients were graded according to the degree of blepharospasm. Level 0 is without spasm. Level 1 is an increase in convulsions caused by external stimuli. Grade 2 is mild spasm, slight twitching of eyelids, and no dysfunction. Grade 3 is moderate spasm, with obvious eyelid spasm and mild dysfunction. Grade 4 is severe spasm, severe blepharospasm, obvious dysfunction, affecting work and life.

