### Sample size calculation

2.6

With reference to previous clinical trials on the application of thunder-fire moxibustion combined with acupressure in the treatment of OMS, the standard deviation was 3.13. The purpose of this trial was to observe the difference in relief of ocular muscle spasm between patients with conventional thunder-fire moxibustion and acupressure. We expect that the treatment group can cause 90% of the changes to be clinically meaningful, in line with the superior effect design of the measurement data, and the sample size formula of the measurement index is as follows: 

. Combined with clinical practice, α = 0.05, β = 0.2, and the table *f* (*α*, *β*) = 7.9 then the calculated sample size is 33 cases in each group. According to the 15% shedding rate, the sample size in each group is 38 cases, and the treatment group and the control group total 76 cases.

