### Statistical analysis

2.8

According to the m-ITT principle, all randomized cases will be included. And there is at least 1 treatment and 1 post-baseline data. The missing data are not filled, and the actual observation values are used for statistical analysis. The measurement data are described by mean, standard deviation, median, and quartile. If the data meets the normal distribution, it is compared with the baseline value at the time of enrollment, and a paired T test is used. Differences in efficacy between the 2 groups will be compared using independent sample *t* tests. If the normal distribution is not satisfied, a non-parametric test is used. The count data is described using a composition ratio. If the normal distribution is satisfied, the changes before and after treatment in the 2 groups are tested by X^2^. If the normal distribution is not satisfied, a non-parametric test is used. The statistical software is SPSS 24.0, when *P* < .05, it showed that the difference is statistically significant.

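### Section 2.8 chooses the count-data test by a normality condition that category counts cannot meet, so the test for the ordered primary outcome is not fixed

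*Protocol article*

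**What the plan says.** Section 2.5.1 of the protocol article defines the primary outcome as three ordered categories. The best is "Cure: the twitching of the eye cells or facial muscles disappears without recurrence within half a year", effective lies in the middle, and the worst is "Ineffective: The degree of spasm of the ocular muscles has not improved". The same section adds an ordinal spasm grade from 0 to 4: "All patients were graded according to the degree of blepharospasm".

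Section 2.8 takes measurement data first, with a paired t test against baseline. It continues "Differences in efficacy between the 2 groups will be compared using independent sample" t tests, with a non-parametric alternative if the data are not normal. It then turns to counts: "The count data is described using a composition ratio". The next sentence reads "If the normal distribution is satisfied, the changes before and after treatment in the 2 groups are tested by" chi-square, and the last sentence of the rule is "If the normal distribution is not satisfied, a non-parametric test is used".

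No sentence assigns a test to the primary outcome by name.

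**The concern.** The normality condition belongs to the measurement data and has been repeated for counts, where it means nothing. A Pearson chi-square needs independent observations and adequate expected counts. It does not need normal data. A rule that turns on an inapplicable condition does not choose a test.

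The rule reaches the primary outcome, which is categorical. Three candidates remain: chi-square, an unnamed non-parametric test, and the t test attached to the word efficacy. If the choice is made once outcomes are visible, the 5% error rate of the main comparison is no longer protected, even if each candidate is valid when fixed in advance.

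Two further questions follow. What does chi-square cost if it is used on the three ordered categories? And does the reference to changes before and after treatment mean that the same patients are counted twice?

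**Working it through.** **Inputs from the protocol article.** Three ordered categories and a 0–4 grade (2.5.1); "α = 0.05, β = 0.2", f = 7.9, SD 3.13, 33 per group before dropout and 38 after (2.6).

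**The plan's own figures.** f = 7.9 agrees with the two-sided (1.960 + 0.842)² = 7.85. 33 × 1.15 = 37.95, hence 38. The extracted text shows no target difference, so 33 cannot be reproduced. Under n = 2·SD²·f/δ² it implies δ = √(2 × 3.13² × 7.9 / 33) = 2.17 on an unnamed scale. Here 33 serves only as the number analysed per arm.

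**Step 1: the rule applied literally.** Cure/effective/ineffective cannot be normal, so the chi-square branch is never reached and the unnamed fallback always applies. If the condition is ignored, chi-square applies. If the efficacy sentence governs, a t test applies. The text does not settle which.

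**Step 2: chi-square between arms on the 2x3 table.** The document gives no category rates, so I assume control rates of 20/50/30% (cure/effective/ineffective). Under proportional odds each cumulative odds is multiplied by the odds ratio (OR). For OR 3:
- Cure: 0.20/0.80 = 0.25; × 3 = 0.75; 0.75/1.75 = 0.429.
- Cure or effective: 0.70/0.30 = 2.333; × 3 = 7; 7/8 = 0.875.
- Treated rates: 0.429 / 0.446 / 0.125.

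Simulation with 200,000 runs, 33 per arm, two-sided 5%, Pearson chi-square (2 df) against the tie-corrected rank-sum test:

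| OR | Chi-square | Rank-sum | Difference (points) |
|---|---|---|---|
| 1 (null) | 5.2% | 5.0% | – |
| 2.5 | 38.9% | 49.0% | 10.1 |
| 3 | 53.1% | 63.9% | 10.8 |
| 3.5 | 65.1% | 75.3% | 10.2 |
| 4 | 74.4% | 83.2% | 8.8 |

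With other assumed control rates (10/60/30, 30/40/30, 15/45/40) at 33 per arm, the difference over the same odds ratios runs from 8.1 to 10.8 points. Size is 4.9% to 5.2% for both tests. At 38 per arm the smallest difference is 7.2 points (81.1% against 88.3%).

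**Step 3: benefit at mainly one boundary.** Same control rates, 33 per arm, treated rates also assumed. The two cut-point odds ratios show how far each case departs from proportional odds; for 45/30/25 they are (0.45/0.55)/0.25 = 3.27 and (0.75/0.25)/2.333 = 1.29.

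| Treated rates (%) | OR, cure | OR, cure or effective | Chi-square | Rank-sum |
|---|---|---|---|---|
| 45/30/25 | 3.27 | 1.29 | about 52% | 37% |
| 50/25/25 | 4.00 | 1.29 | 69% | 47% |
| 20/72/8 | 1.00 | 4.93 | 57% | 30% |

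Here chi-square is the more powerful test.

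**Step 4: chi-square on before against after counts.** For a binary item with proportion p, n patients and within-patient correlation ρ, the true variance of the difference is 2p(1−p)(1−ρ)/n, but chi-square uses 2p(1−p)/n. The true size is therefore about 2Φ(−1.96/√(1−ρ)): 0.019 at ρ = 0.3, 0.0056 at 0.5 and 0.0003 at 0.7. Simulation with 38 patients gives 0.019, 0.006 and 0.0005. For a 25-point change at ρ = 0.3 to 0.5, power is 64–67%, against 76–92% for McNemar.

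**The case against.** **The fallback may be the right test.** Counts are never normal, so the plan read literally always goes to a non-parametric test. If that is a rank-sum test, the order is used. This stands as far as it goes: a reader might infer that the plan wastes the order, but that holds only if the named chi-square is used. It does not rescue the rule, because the only test named for counts would then never apply and the one that applies has no name. An article may leave a test's name to the analysis plan. It may not fix a condition that cannot be evaluated.

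**Chi-square is not an error here.** Between arms it holds its size, and step 3 shows that it can win. A reader might infer that it is always the less powerful choice. The documents give no category rates, and the ranking depends on where the benefit falls. This objection stands in full.

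**The pairing error does not reach the primary outcome.** A reader might infer from the before-and-after wording that the primary test counts each patient twice. Cure/effective/ineffective is already a classification of change and has no baseline value, and the sentence can equally mean change categories compared between arms. Pairing matters only if something measured twice, such as the 0–4 grade, is tabulated before against after. Even then, positive correlation makes the test conservative, so no excess of false positives is shown.

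**The t-test sentence may govern.** It stands among the rules for measurement data, and section 2.6 also sizes the trial on measurement data. That reading is possible, but it adds a third candidate and does not settle the choice.

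**Conclusion.** The concern holds in a limited form, as something that should be fixed. The normality condition for count data is stated wrongly in the current text. Together with the efficacy sentence, it leaves the test for the ordered primary outcome unfixed before the data are seen. That part rests on the wording alone.

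The cost of ignoring the order, about 8 to 11 points of power, is conditional on 33 per arm, the four assumed sets of control rates, proportional odds and odds ratios of 2.5 to 4. It reverses when the benefit is confined to one boundary. The document does not support calling chi-square invalid for the between-arm comparison, nor saying that the primary test has a wrong standard error.

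**What to change.** Reword section 2.8 before any outcome data are examined:

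- Delete the normality condition for count data.
- Name one between-arm test for cure/effective/ineffective that uses the order: Wilcoxon-Mann-Whitney, or proportional-odds regression reporting a common odds ratio with a 95% CI.
- State which outcomes the between-group t test covers, so that it no longer competes for the primary outcome.
- Keep chi-square or Fisher for binary or nominal items.
- For within-group change in categories, use a paired method and report it as descriptive only.

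The cost is a rewording, with no new data, visits or patients. The price is some loss of power if the benefit turns out to lie at one category boundary (37% against about 52%, 47% against 69% and 30% against 57% in the cases above). If the investigators expect such a pattern, they should say so now and choose the test accordingly.

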### Data management

2.9

Information obtained from the evaluation of each participant will be recorded on a paper print-out. The information will then be handwritten on a paper document case report form and entered into an Excel file for future statistical analyses. In accordance with the Personal Information Protection Act, the names of all participants will not be disclosed, and a unique identifier number given during the trial will be used to identify participants. All of the participants will be informed that the clinical data obtained in the trial will be stored in a computer and will be handled with confidentiality. The participants written consent will be stored by the principal investigator (Fig. 2).

**Figure 2 F2:**
[figure not shown]
Study design flow chart.

## Discussion

3

OMS is an unexplained and involuntary muscle spasm and convulsions in the innervation area of the facial nerve, which is more common in the middle-aged and elderly people, and is more common in the 50 to 70 age group, and more women than men.^[9]^ In the early stage of the patient, the number of blinks increased, and the eyelids became heavy, and paroxysmal opening of the eyes often occurred during gaze. Because the control center of blepharospasm is not yet clear, there are no targeted drugs.^[10]^ At first, blepharospasm was considered a manifestation of mental illness, so antipsychotic drugs were used. It has recently been discovered that the efficacy of these drugs is not due to the treatment of mental illness, but to the motor system. Most patients do not respond partially or completely to medication. The best case is a partial short-term relief. There are individual differences in the response of OMS patients to various drugs, but there is no way to predict which patient will respond to which specific drug. Tricyclic antidepressants do not directly affect blepharospasm, but they are helpful for patients with aggravated symptoms of depression.^[11]^ Various drugs have shown partial efficacy for blepharospasm. The goal of medication is to improve symptoms and reduce complications. Botulinum toxin can improve orbicularis oculi muscle spasm and autonomic symptoms. The efficacy of botulinum toxin injection treatment is generally temporary, requiring repeated treatment for a long time. Common complications of botulinum toxin injection include drooping eyelids and weakness of facial muscles. Common complications of surgical treatment include scars and edema. Resection of the orbicularis oculi muscle is permanent.

At present, TCM nursing technology plays an important role and advantage in preventing health care, promoting rehabilitation, and alleviating pain. Thunder-fire moxibustion belongs to the nursing technology of TCM, which has the function of warming and ventilating.^[12]^ It can dredge the eye blood and warm the meridians through the warming effect; and acupressure is the earliest application of massage therapy, which belongs to the external treatment of TCM category.^[13]^ Acupressure specifically refers to the use of the doctors hands and the use of standardized movement techniques to adjust the bodys physiological functions and pathological changes, to achieve the functions of dredging the meridians, promoting blood circulation and removing blood stasis, adjusting viscera and blood, and improving the bodys ability to resist disease.^[7,14]^ Related literature confirms that the use of thunder-fire moxibustion or acupressure can treat or delay the development of ocular muscle spasm. At present, the clinical application of thunder-fire moxibustion and acupressure nursing technology for the treatment of ocular muscle spasm has irregular operation procedures and inconsistent treatment frequency and time, which may be the reason for affecting the evaluation of efficacy. This study proposes a hypothesis, intends to adopt a randomized controlled clinical research method, standardize the operation steps, and provide evidence-based medical evidence for the improvement of OMS in TCM nursing technology. At the same time, we also hope that this study can provide simple and easy-to-promote nursing technology for the clinical diagnosis and treatment of OMS.
